## Abstract

**Introduction:**

Radical chemoradiotherapy represents the gold standard for locally advanced cervical cancer. However, despite significant progress in improving local tumour control, distant relapse continues to impact overall survival. The development of predictive and prognostic biomarkers is consequently important to risk-stratify patients and identify populations at higher risk of poorer treatment response and survival outcomes. Exploratory study of using Magnetic resonance Prognostic Imaging markers for Radiotherapy In Cervix cancer (EMPIRIC) is a prospective exploratory cohort study, which aims to investigate the role of multiparametric functional MRI (fMRI) using diffusion-weighed imaging (DWI), dynamic contrast-enhanced (DCE) and blood oxygen level-dependent imaging (BOLD) MRI to assess treatment response and predict outcomes in patients undergoing radical chemoradiotherapy for cervical cancer.

**Methods and analysis:**

The study aims to recruit 40 patients across a single-centre over 2 years. Patients undergo multiparametric fMRI (DWI, DCE and BOLD-MRI) at three time points: before, during and at the completion of external beam radiotherapy. Tissue and liquid biopsies are collected at diagnosis and post-treatment to identify potential biomarker correlates against fMRI. The primary outcome is to evaluate sensitivity and specificity of quantitative parameters derived from fMRI as predictors of progression-free survival at 2 years following radical chemoradiotherapy for cervical cancer. The secondary outcome is to investigate the roles of fMRI as predictors of overall survival at 2 years and tumour volume reduction across treatment. Statistical analyses using regression models and survival analyses are employed to evaluate the relationships between the derived parameters, treatment response and clinical outcomes.

**Ethics and dissemination:**

The EMPIRIC study received ethical approval from the NHS Health Research Authority (HRA) on 14 February 2022 (protocol number RD2021-29). Confidentiality and data protection measures are strictly adhered to throughout the study. The findings of this study will be disseminated through peer-reviewed publications and scientific conferences, aiming to contribute to the growing body of evidence on the use of multiparametric MRI in cervical cancer management.

**Trial registration number:**

NCT05532930.

STRENGTHS AND LIMITATIONS OF THIS STUDYNovel imaging approach: Multiparametric functional MRI (fMRI) including T2, diffusion-weighed imaging, dynamic contrast-enhanced and blood oxygen level-dependent-MRI.Temporal data: fMRI obtained prior, during and at the end of chemoradiotherapy will capture longitudinal changes in tumour and fMRI-derived parameters.Parallel molecular analysis: Tissue and liquid biopsies (circulating tumour cells and circulating tumour DNA) will be collected and independently analysed to assess hypoxic and tumour burden respectively and correlated with fMRI sequences.Integrated design: fMRI and molecular samples are collected during chemoradiotherapy with limited additional appointments or effort required for enrolled patients, allowing for smooth translation of imaging and biopsy protocol into wider clinical practice.Single-site study: Patient recruitment is limited to eligible patients referred for chemoradiotherapy at a single cancer centre.

## Introduction

Cervical cancer is the fourth most common cancer affecting women worldwide.^1^ While surgery is suitable for early-stage disease, advanced stage presentations require a combination of chemoradiotherapy (CRT) and image-guided brachytherapy boost as the standard of care. Although local control rates are promising (92% at 5 years), the impact of metastatic disease on overall survival highlights the need to identify high-risk populations with poorer treatment outcomes.^2^ To address this, predictive and prognostic biomarkers are needed.

The use of predictive biomarkers derived from imaging can potentially guide treatment decisions and improve outcomes. Imaging biomarkers are advantageous as they are non-invasive, allow for multiple assessments and provide a comprehensive evaluation of a tumour in its entirety. Unlike biopsies, imaging biomarkers provide valuable spatiotemporal data, which can capture evolving intratumour heterogeneity to better predict tumour control probability.^3^

MRI holds promise as a source of imaging biomarkers for cervical cancer. Traditional T1-weighted and T2-weighted anatomical MRI techniques are commonly used for staging, diagnosing and monitoring cervical cancer.^4^ Additionally, advanced MRI techniques, known as functional MRI (fMRI), can provide valuable biological data. These techniques include diffusion-weighted imaging (DWI), which measures cellular density using water motion assessment; dynamic contrast-enhanced imaging (DCE), which assesses blood flow and vascular permeability; and blood oxygen level-dependent imaging (BOLD), which measures changes in tissue oxygenation. By leveraging these advanced techniques, fMRI may have a role in offering predictive and prognostic biomarkers for cervical cancer.^5^

This has been clarified in a systematic review, which details prospective studies using different fMRI techniques in cervical cancer. DWI and DCE-MRI represent the most used techniques, followed by BOLD-MRI. Furthermore, the majority of studies evaluated a single technique rather than a combination. This has led to a lack of consensus confounded by ‘multiple interacting factors, including histology, grade, hypoxia, vascularity and cellularity that can influence fMRI-derived parameters’. To account for this, future studies will need to employ combinations of fMRI techniques to generate ‘a more holistic assessment of the tumour, simultaneously assessing multiple tumour features to improve outcome prediction. Refinement of fMRI as a predictive and prognostic marker can be improved further by combining clinicopathological scoring and or genomic signatures for hypoxia.^6^

In addition to a multiparametric approach, fMRI needs to be repeated across treatment to discern tumour response and relate it to fMRI-derived parameters. Spatial data can also be acquired—an example of which DCE-MRI can identify a ‘functional risk volume’ within the tumour associated with poorer response to treatment. Tumours with a ‘functional risk volume’ displayed poor vascularity and tumour permeability.^7^ More recently, a study demonstrated combining DWI-derived and DCE-derived parameters to describe the ‘hypoxic fraction’ of cervical tumours linking this to disease-free survival.^8^

The Exploratory study of using Magnetic resonance Prognostic Imaging markers for Radiotherapy In Cervix cancer (EMPIRIC) study aims to build on previous studies and address the gaps in the current evidence base by performing multiparametric fMRI (DWI, DCE and BOLD-MRI) across treatment in patients with cervical cancer, alongside collection of blood samples for circulating tumour cell (CTC) and circulating tumour DNA (CtDNA) and tissue biopsies to facilitate parallel molecular analysis. This holistic approach to tumour characterisation will provide the tools to generate a meaningful predictive and prognostic model for personalised radiotherapy for cervical cancer.

## Method

### Study design and setting

EMPIRIC (ClinicalTrials.gov NCT05532930) is a prospective, non-randomised, single-centre (Mount Vernon Cancer Centre, UK) observational study in which patients with locally advanced cervical cancer fit for CRT are included.

The study aims to recruit 40 patients in total over an accrual period of 36 months at Mount Vernon Cancer Centre, UK. The study started in August 2022 and is actively recruiting. It is a single cohort study, where patients undergoing CRT (45 Gy in 25# of external beam radiotherapy with concurrent weekly cisplatin, followed by image-guided brachytherapy boost) for cervical cancer undergo fMRI before, during and at the end of their treatment, along with analysis of CTC, CtDNA and tissue biopsies. Online supplemental table 1 provides an overview of the study schedule.

10.1136/bmjopen-2023-077390.supp1Supplementary data

### Patient and public involvement and engagement

As part of trial development, evaluation and input from lay members of the funding committee were collected. Patients reviewed in outpatient clinics were consulted in addition to a patient advocate. We are continuing to gather patient feedback from enrolled participants and their relatives on the acceptability of added interventions (fMRI, blood tests and biopsies).

### Consent and withdrawal

Written informed consent will be obtained for all patients included in the study before they are registered by a clinician within the EMPIRIC research team.

All patients will be informed of the purpose of the investigation and the possible risks and side effects involved with the extra scans and contrast administration through patient information sheets and at the time of consent. Patients will be informed as to the strict confidentiality of their patient data, but that their medical records, including trial imaging, may be reviewed for study purposes by authorised individuals other than their treating physician. Participants are free to withdraw at any time, or the discretion of the EMPIRIC chief or principal investigator. In the event of withdrawal, any data that have been collected will be kept and potentially included in any analyses.

### Eligibility criteria

The inclusion criteria are as follows:

Histologically confirmed International Federation of Gynecology and Obstetrics (FIGO) stage Ib2–IVa squamous, adeno or adenosquamous carcinoma of the cervix.Clinically and/or radiographically documented measurable disease with at least one site of disease unidimensionally measurable as per Response Evaluation Criteria in Solid Tumours (RECIST) 1.1All detectable disease including pelvic/para-aortic nodes encompassable within radical high-dose radiation field.Deemed suitable and fit for radical CRT.Eastern Cooperative Oncology Group (ECOG) performance status 0–1.Aged 18 and over.Documented negative pregnancy test (if applicable).Capable of providing written or witnessed informed consent according to International Council for Harmonisation of Technical Requirements for Registration of Pharmaceuticals for Human Use (ICH)/Good Clinical Practice (GCP) and national/local guidelines prior to registration.

The exclusion criteria are as follows:

Previous pelvic malignancy (regardless of interval since diagnosis).Previous malignancy not affecting the pelvis (except basal cell carcinoma of the skin) where disease-free interval is less than 10 years.Evidence of distant metastasis, that is, any non-nodal metastasis beyond the pelvis.Previous pelvic radiotherapy.Prior diagnosis of Crohn’s disease or ulcerative colitis.Uncontrolled cardiac disease (defined as cardiac function which would preclude hydration during cisplatin administration).Previous record of allergic reaction to gadolinium-based contrast media and any other contraindication to MRI.Any psychological, familial, sociological or geographical condition potentially hampering compliance with the study protocol and follow-up schedule; those conditions should be discussed with the patient before registration in the study.Participation in any other interventional trials.

### fMRI assessment

Each multiparametric fMRI scan will consist of sequences: DCE-MRI, DWI-MRI, BOLD-MRI, quantitative T1-weighted and T2-weighted MRI and will be carried out at three time points- prior to CRT (RT planning), week 2 of CRT (fraction 10) and week 5 of CRT prior to brachytherapy (fraction 25). Delineations of the gross tumour volume (GTV) using T2-weighted MR sequences for each case will be performed by a clinical oncologist and verified by a consultant radiologist. The GTV tumour volume reduction rate (TVRR) will be determined between these three time points as defined on anatomic sequences. Kinetic modelling will be applied in DCE-MRI images to assess quantitative kinetic parameters in the GTV related to blood volume, blood flow, interstitial volume and tissue permeability. DWI-MRI sequences will be used to calculate ADC maps to provide information related to tumour cellularity and necrosis. Signal changes on BOLD-MRI sequences will be used to calculate the T2 relaxation rate reflecting intravascular deoxyhaemoglobin concentration, and therefore, providing information related to tumour oxygenation. Anatomic T1 and T2 imaging will be used for radiomic feature extraction and textural analysis through quantitative mapping.

The details of each MRI and radiomic parameter are summarised in table 1.

**Table 1 T1:** fMRI sequences with corresponding parameters used to assess cervical tumour response during radical chemoradiotherapy

Imaging	Parameters	Biological correlates
DCE-MRI	Extravascular extracellular space volume fraction V_e_ (%)	Blood volume, blood flow, interstitial volume and tissue permeability
	Transfer constant K^trans^ (/min)	
	Rate Constant k_ep_ (/min)	
	Blood volume fraction v_p_ (%)	
DWI-MRI	Apparent diffusion coefficient ADC (um^2^/s)	Tumour cellularity, architectural complexity and necrosis
BOLD-MRI	BOLD-based reversible transverse relaxation rate R2^*^ (/s)	Intravascular deoxyhaemoglobin concentration
T1 and T2 weighted MRI	Relaxation times (/s)	Tissue physical characters affecting water relaxation and anatomical information
T2-weighted±DWI MRI (Grey level co-occurrence matrix)	Second-order Haralick textural radiomic features	Intratumoural heterogeneity

BOLD, blood oxygen-level dependent; DWI, diffusion-weighed imaging; fMRI, functional MRI.

### Translational biological assessment

Tumour tissues from the diagnostic biopsy and a second biopsy taken at the time of brachytherapy will be collected. The unstained biopsy slides will be stained for immunohistochemical markers of hypoxia (CA IX, GLUT-1), vascularity (VEGF) and epithelial mesenchymal transition (CD44, SOX-2). These molecular markers at various time points will be correlated with imaging parameters and evaluated independently and in combination with respect to prognostic impact. Peripheral blood samples will be taken at the three imaging time points (pre-CRT, fraction 10 and fraction 25 of CRT) for analysis of CTCs. CTCs will be isolated from peripheral blood samples via an optimised enrichment technique using CD45 antibody. Based on branched DNA signal amplification technology, CTCs will be classified into three subpopulations with respect to metastatic potential using epithelial mesenchymal transition markers: epithelial CTCs (EpCAM or CK8), mesenchymal CTCs (vimentin or TWIST) and mixed phenotype CTCs (both markers). The CTC phenotype ratio at various time points will be correlated with imaging parameters and evaluated independently and in combination with respect to prognostic impact (progression-free survival and overall survival).

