### Radiotherapy-related assessment

Quantitative MR parameters (BOLD signals complimented by perfusion information from DCE-MRI and cellularity information from DWI-MRI) derived at various time points during treatment will be used to create a high-risk map that can be delineated and registered onto the anatomic sequences of the planning MRI performed at the time of image-guided brachytherapy. The map will be used to delineate a residual high-risk tumour volume (HTV-T_res_) within the high-risk clinical target volume (HR-CTV) for brachytherapy. Original treatment plans will then be reoptimised escalating the HTV-T_res_ to 140% of the original HR-CTV prescription (9.8 Gy/fraction) with the aim of achieving the volume of HTV-T_res_ receiving 140 Gy (HTV-T_res_V_140_) ≥90% and 98% of HTV-T_res_ to receive over 100 Gy (D_98_≥100 Gy) while maintaining HR-CTV coverage and organ-at-risk dose-volume histograms within tolerance.

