#### Secondary outcomes

To evaluate sensitivity and specificity quantitative parameters derived from DCE-MRI, DWI-MRI and BOLD-MRI as predictors of overall survival at 2 years in patients with locally advanced cervical cancer after CRT.To evaluate sensitivity and specificity quantitative parameters derived from DCE-MRI, DWI-MRI and BOLD-MRI as predictors of the TVRR in response to CRT of patients with locally advanced cervical cancer.To apply radiomics for derivation of textural imaging features as predictors of progression-free (local, nodal, systemic), overall survival and TVRR after CRT for cervix cancer.To correlate temporal changes in quantitative MRI parameters during CRT with molecular markers from tissue biopsies and CTCs isolated from peripheral blood samples.To explore the feasibility of using quantitative MRI parameters to provide a roadmap in identifying high-risk regions for potential dose escalation with radiotherapy.

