### Statistical analysis

Using logistic and Cox regression models the study will evaluate:

Different thresholds and temporal changes of fMRI parameters (DCE-MRI, DWI-MRI and BOLD-MRI) at various time points during cervical CRT can predict progression-free (local, nodal, distant) survival.Different thresholds and temporal changes of fMRI parameters (DCE-MRI, DWI-MRI and BOLD-MRI) at various time points during cervical CRT can predict response to treatment as defined by TVRR.Different thresholds and temporal changes of fMRI parameters (DCE-MRI, DWI-MRI and BOLD-MRI) at various time points during cervical CRT can predict overall survival.Different radiomics features can predict response to cervical CRT in terms of TVRR, progression-free (local, nodal, distant) survival and overall survival.Different thresholds and temporal changes of fMRI parameters (DCE-MRI, DWI-MRI and BOLD-MRI) at various time points during cervical CRT can predict changes in immunohistochemical markers of hypoxia and epithelial mesenchymal transition.

For each of the above regression analyses, a univariate logistic regression reporting the OR with 95% CI and p value from the likelihood ratio test will be performed. All covariates (fMRI parameters and radiomic features in table 1) and demographics) with a p<0.1 will be entered into a multivariate, forward conditional logistic regression and subsequently a p<0.05 will be considered statistically significant. The utility of the final prognostic model will be evaluated using sensitivity, specificity and area under the receiver operating characteristic curve.

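### The regression on paired tissue-marker change is defined only in patients whose brachytherapy biopsy still holds scorable tumour, a plausibly response-dependent subset of unstated size

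*Protocol article*

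**What the plan says.** The Translational biological assessment section fixes two tissue time points: "Tumour tissues from the diagnostic biopsy and a second biopsy taken at the time of brachytherapy will be collected". The slides are stained for hypoxia markers (CA IX, GLUT-1), a vascularity marker (VEGF) and markers of epithelial mesenchymal transition (CD44, SOX-2).

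Study design and setting places brachytherapy after external beam treatment: "45 Gy in 25# of external beam radiotherapy with concurrent weekly cisplatin, followed by image-guided brachytherapy boost".

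The last item listed under Statistical analysis asks whether thresholds and temporal changes of fMRI parameters "can predict changes in immunohistochemical markers of hypoxia and epithelial mesenchymal transition". It is the only item in that list with a tissue marker as outcome.

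The corresponding secondary outcome is wider: "To correlate temporal changes in quantitative MRI parameters during CRT with molecular markers from tissue biopsies and CTCs isolated from peripheral blood samples". The blood sampling that serves it is separate from tissue: "Peripheral blood samples will be taken at the three imaging time points (pre-CRT, fraction 10 and fraction 25 of CRT) for analysis of CTCs". The Translational section also plans to correlate tissue markers at each time point with imaging, which includes the diagnostic biopsy.

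**The concern.** A change in a tumour-cell marker can be scored only if both samples contain tumour. The first does by definition, since histological confirmation is an entry criterion. The second is taken after a full course of external beam radiotherapy with cisplatin, when some patients may have no tumour left to score. Those patients have no outcome value and leave the regression.

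This differs from ordinary missing data in two ways. First, whether the outcome exists plausibly depends on response to treatment, and response (as tumour volume reduction rate, TVRR) is something the same fMRI parameters are meant to predict. Selection is therefore linked to the predictor. Secondly, no later missing-data rule can supply a tumour marker score where there is no tumour, so the limit lies in the choice of outcome.

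At stake is how the result is read. A weak association could mean that fMRI does not track tumour biology, or that selection distorted the comparison. A strong one could also be partly produced by selection. Whether tumour remained at brachytherapy is itself informative about response, and the listed analyses do not use it.

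**Working it through.** **What the plan gives.** It states no number of evaluable pairs and no share of patients with scorable tumour at brachytherapy, so there is no figure of its own to reproduce on this point. The only documented input is the sample size of 40 (Sample size and power). Everything else below is an assumption shown over a range.

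**Step 1: pairs.** Pairs = 40 × (1 − share not scorable), taking every patient to have a second biopsy. For assumed shares of 20%, 40% and 60%:
- 40 × 0.80 = 32
- 40 × 0.60 = 24
- 40 × 0.40 = 16

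**Step 2: what those numbers can detect, ignoring bias.** The smallest correlation detectable at two-sided 0.05 with 80% power (both my assumptions; the plan has no power calculation) is tanh[(1.96 + 0.84)/√(n − 3)]:
- n = 40: 0.43
- n = 32: 0.48
- n = 24: 0.55
- n = 16: 0.65

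**Step 3: effect of selection on the association.** Let X be fMRI change, Y marker change and R response, all standard normal. Keep the less-responding fraction f, that is R below c = Φ⁻¹(f). With λ = φ(c)/f, the variance of R falls by k = λ(λ + c). The correlation of X and Y among those kept is

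(r_XY − k·r_XR·r_YR) / √[(1 − k·r_XR²)(1 − k·r_YR²)].

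For a 20% loss, f = 0.80, c = 0.842, λ = 0.350 and k = 0.350 × 1.192 = 0.417. For 40% and 60% loss, k = 0.578 and 0.688. Worked example at 20% loss with all correlations 0.5: (0.5 − 0.417 × 0.25)/(1 − 0.417 × 0.25) = 0.396/0.896 = 0.44.

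True r_XY = 0.50 throughout:

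| Assumed link of response to X and Y | 20% lost | 40% lost | 60% lost |
|---|---|---|---|
| Y is response itself (r_XR = 0.5, r_YR = 1) | 0.40 | 0.35 | 0.31 |
| r_XR = r_YR = 0.5 | 0.44 | 0.42 | 0.40 |
| r_XR = r_YR = 0.3 | 0.48 | 0.47 | 0.47 |
| r_XR = 0.5, r_YR = 0 | 0.53 | 0.54 | 0.55 |

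The first row gives the largest fall and holds only if marker change and response are the same variable. When response acts as a third variable the fall is smaller, can be slight, and in the last row becomes a rise.

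**Step 4: what is outside the problem.** Blood samples for circulating tumour cells are drawn at three time points and need no residual tumour. The diagnostic biopsy exists whatever the response. Only analyses that use the second biopsy's marker score are exposed, and the change regression is the one listed under Statistical analysis.

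**The case against.** The strongest reply has four parts.

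- **Scope.** The molecular secondary outcome also rests on circulating tumour cells and on markers in the diagnostic biopsy, and correlating markers at each time point with imaging is already planned. This stands. A reader might infer that the whole molecular objective fails; the documents do not support that.
- **Who is selected.** A reader might infer that the paired analysis covers poor responders only. That does not follow. The second biopsy comes before the brachytherapy boost has been completed, and the article nowhere equates tumour at that point with resistance. It plans for residual disease there: "The map will be used to delineate a residual high-risk tumour volume". That volume is defined on imaging, however, and does not show that every biopsy will hold scorable tumour. What remains is a response-dependent subset of unknown size.
- **Direction and size.** A reader might infer that the association must be attenuated. The table shows that it need not be, and every input except the 40 is assumed. This part stands as well.
- **Level of detail.** Handling of non-evaluable samples may sit in the full protocol or analysis plan, and the study is exploratory with validation left to later work. The absence of such a rule is therefore no finding. The point that remains is that the stated outcome is undefined in some patients for a reason tied to treatment response, which a handling rule cannot repair.

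**Conclusion.** The concern holds for the paired tissue-marker change regression and no further. Its outcome is defined only where the brachytherapy biopsy contains scorable tumour, so a complete-case fit conditions on a post-treatment variable plausibly linked to the fMRI predictors. With an assumed 20% to 60% not scorable, the cost in numbers is a fall from 40 pairs to between 32 and 16. The accompanying bias has no fixed direction: under the assumptions tabulated, a true correlation of 0.50 becomes anything from 0.31 to 0.55.

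The conclusion rests on two premises that the article does not quantify: that some second biopsies will lack scorable tumour, and that this is related to response. Both are plausible after 45 Gy with cisplatin. This is a worthwhile low-cost improvement to one secondary analysis. It does not affect the primary outcome.

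**What to change.** Wording changes only, in the analysis section or the analysis plan:

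1. Add an analysis on all patients with a second biopsy: viable tumour at brachytherapy (yes/no), predicted from pre-CRT and fraction-10 fMRI parameters.
2. Keep the paired marker-change regression, but report it as applying to patients with scorable residual tumour and limit its conclusion to them. Give the counts scorable and not scorable, and compare baseline fMRI and TVRR between the two groups.
3. Report the correlation of diagnostic-biopsy markers with pre-CRT fMRI, already within the Translational section's plan, as the tissue analysis free of this selection.

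No new biopsy, assay or visit is needed. The downside is that a biopsy can miss residual tumour, so the yes/no outcome carries sampling error, which should be acknowledged when it is reported. Patients with no second biopsy at all stay outside item 1 and should be counted separately.
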